### Data management

The collected data will be password-protected in a cabinet. The cabinet's passcode will only be known by the PI. The research team will take precautions to keep the data private before, during, and after the trial. No individual's details will be revealed.

### Protocol amendments

To determine whether the protocol needs to be revised, the research team will conduct a review. University of Houston-Downtown Committee for the Protection of Human Subjects will receive the modified protocol, and the participants will be notified as well.

### Statistical analysis

We will summarize the characteristics of the participants at baseline by treatment arm using descriptive statistics. Specifically, we will use mean (standard deviation) for normal (or roughly normal) continuous data, and medians (25th percentile, 75th percentile) for non-normal continuous data, and frequency (percentages) for categorical data. The two-sample *t-*test and chi-square test (or Fisher's exact test, as appropriate) will be used to examine differences by the two arms at baseline.

The primary outcome will be assessed according to intention-to-treat (48) principles. We will use a mixed model for repeated measures (MMRM) (49) to model the change from baseline at each post*-*baseline visit in two arms, with each of the primary outcomes as dependent variable. For each of the outcome, using MMRM, we will compare the difference between the treatment vs. placebo arm in change in mean response from baseline at last visit. The likelihood-based MMRM can handle missingness in the responses when the responses are missing at random (50).

For the secondary outcome, we will calculate rates of recruitment (defined as the number of consented individuals divided by the number of eligible individuals), completion (defined as the percentage of completion at baseline and follow-up visits), adherence (defined as participants' completed sessions divided by the number of offered sessions), and adverse events (in two forms, total number and number per participant).

The statistician is not part of the research team and is not aware of the group assignment. All analyses will be performed using R statistical software (version 2020) (36). A two-sided *P*-value of 0.05 or less will be considered statistical significance.

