### Sample size

The sample size per arm is calculated using longpower R package (a package for longitudinal data sample size calculation) (37, 38). For a longitudinal design with two arms (with allocation ratio = 1:1) focusing on the difference in change from baseline at the last visit in SF-MPQ-2 total score, with a power of 0.8 and significance level of 0.05 (two-sided), a dropout rate of 25% at post-baseline visits in both arms, a compound symmetric within-individual correlation matrix with an intraclass correlation coefficient of 0.8 in both arms, a standard deviation of 2 for change in score from baseline at last visit (assuming the same in both arms), and effect size of 1, the sample size per arm is 71 (142 in total).

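### The primary MMRM is described as a model of change from baseline with no baseline term named; writing baseline into the model is a modest but free gain in precision

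*Protocol article*

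**What the plan says.** The Statistical analysis section of the Protocol article specifies a "mixed model for repeated measures (MMRM) (49) to model the change from baseline at each" post-baseline visit in the two arms, "with each of the primary outcomes as dependent variable". The comparison of interest is treatment versus "placebo arm in change in mean response from baseline at last visit". Missing responses are left to the likelihood under a missing-at-random assumption. Arm and visit are the only terms that can be read from the description, and baseline appears only as the value from which change is measured.

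The Primary outcome section has all three outcomes measured at baseline (after consent, before randomisation), at the sixth visit and 12 weeks later. The Sample size section works on change in the SF-MPQ-2 total score at the last visit. It assumes an SD of change of 2, an effect size of 1, "a dropout rate of 25% at post-baseline visits in both arms" and "a compound symmetric within-individual correlation matrix with an intraclass correlation coefficient of 0.8 in both arms".

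**The concern.** Every randomised participant should have a baseline score, and that score predicts the later ones. A change score uses it with a fixed coefficient of 1. When the correlation between visits is below 1, this subtracts too much, and the change stays negatively related to baseline. A model that estimates the coefficient removes that leftover variation without bias or extra data.

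Two things are at stake. The first is precision on all three primary outcomes. The second is the missing-data argument: under a change-score model without baseline, missingness may depend on arm and on observed changes, but dependence on baseline severity is not conditioned on. With equal variances and a correlation of 0.8, the slope of change on baseline is 0.8 − 1 = −0.2. Dropout that depends on severity differently in the two arms could therefore shift the contrast. Putting baseline in the model covers that mechanism.

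The wording also leaves the response variable open. One phrase makes change the modelled quantity, and another makes the outcome itself the dependent variable.

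**Working it through.** **Inputs (Sample size section).** SD of change 2, difference 1 (effect size read as one raw point), two-sided alpha 0.05, power 0.80, 25% dropout, correlation 0.8. (1.960 + 0.842)² = 7.849.

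**The plan's own figure.** Without dropout, n per arm = 2 × 4 × 7.849 / 1² = 62.79. If one response visit is fully retained and the later ones are 75% retained, the MMRM inflation factor is 0.8² + (1 − 0.8²)/0.75 = 0.64 + 0.48 = 1.12. Then 62.79 × 1.12 = 70.33, which rounds up to 71, so the stated figure reproduces. The fully retained visit could be baseline or the sixth visit, so 71 does not show which model is intended.

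**Variance with and without baseline.** Read 0.8 as the raw-score correlation, with equal variances at all visits. The raw variance is 4 / [2(1 − 0.8)] = 10.
- Change score: 10 × 2(1 − 0.8) = 4.0.
- Baseline-adjusted: 10 × (1 − 0.8²) = 3.6.
- Ratio (1 + 0.8)/2 = 0.90, a 10% saving.

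**Case A: 25% miss both post-baseline visits.** The variance of the contrast is 2v/(71 × 0.75).
- Change score: 8/53.25 = 0.1502; power 73.2%; 62.79/0.75 = 83.7, so 84 per arm for 80%.
- Baseline-adjusted: 7.2/53.25 = 0.1352; power 77.6%; 62.79 × 0.9/0.75 = 75.3, so 76 per arm.

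**Case B: all loss falls after the sixth visit.** The last-visit variance is v × [r² + (1 − r²)/0.75], where r is the correlation between the two post-baseline responses in the model used.
- Change score: r = 0.2/0.4 = 0.5; 4.0 × 1.25 = 5.0; contrast variance 10/71 = 0.1408; power 76.0%; 79 per arm.
- Baseline-adjusted: r = 0.16/0.36 = 0.444; 3.6 × 1.2675 = 4.563; contrast variance 0.1285; power 79.7%; 72 per arm.

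In both cases the constrained longitudinal model gives the baseline-adjusted figures.

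**Score as response, separate baseline mean in each arm.** Power is 74.3% in case A and 76.3% in case B. Making the score the response therefore recovers little unless the arms share a baseline mean.

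**Sensitivity.** The baseline-to-last correlation is not given separately. With SD of change held at 2 and 25% missing both visits, the change-score model stays at 73.2%:

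| Correlation (assumed, except 0.8) | Variance saving | Adjusted power at 71 per arm |
|---|---|---|
| 0.5 | 25% | 84.6% |
| 0.7 | 15% | 79.9% |
| 0.8 | 10% | 77.6% |
| 0.9 | 5% | 75.4% |

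The documents give no correlation for LEFS or SF-36, so the saving for those outcomes is not known.

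**The case against.** The strongest reply is that this is a condensed article, that covariate lists and analysis sets commonly sit in an analysis plan that is not shown, and that silence on baseline does not exclude it. That stands as far as it goes. The wording also permits a model with the score as response and change as a contrast of visit means, and the sample size is compatible with baseline as a fully observed response.

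A second reply is that an unadjusted change-score MMRM is a valid analysis. That is also right. Chance baseline imbalance is a small matter here: at a correlation of 0.8 only about 0.2 of an imbalance carries through, with opposite sign, and the estimate is unbiased over randomisation. Adjustment is a gain in efficiency and does not correct an error.

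A reader might infer that the plan drops participants who have no post-baseline visit and so undercuts its statement that "The primary outcome will be assessed according to intention-to-treat (48) principles". The documents do not support this. Nothing in them excludes anyone. Under a change-score reading such participants would add nothing to the likelihood, but a baseline covariate would not bring them back either. A constrained model keeps them in the likelihood, yet in case A it has the same power as covariate adjustment (77.6%).

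What remains is that the article does more than name a method. It states the modelled quantity and the contrast, in wording that leads naturally to the less precise model.

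**Conclusion.** The point holds as a free improvement and as an ambiguity to settle. As described, the primary model names no baseline term and does not make clear whether score or change is the response. If it is run on change scores without baseline, the variance at the plan's correlation is 4.0 where 3.6 is attainable. The cost is about 4 power points: 73% against 78% if 25% miss both post-baseline visits, and 76% against 80% if loss occurs only after the first.

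These figures rest on reading 0.8 as the raw-score correlation, equal variances over time, and a one-point difference. The gain is modest. At 0.8 it does not restore 80% power when 25% miss both visits, because most of that shortfall comes from how dropout enters the sample size. The missing-data point is qualitative: without baseline, the missing-at-random argument cannot use baseline severity.

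**What to change.** In the Statistical analysis section, state which variable is the response and that baseline enters the model for all three primary outcomes, in one of two forms:

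- change (or score) at the two post-baseline visits as response, with arm, visit, arm-by-visit, baseline score and baseline-by-visit; or
- baseline, sixth-visit and 12-week scores all as responses in a constrained longitudinal model, with a baseline mean common to both arms, arm-by-visit effects after baseline and an unstructured covariance.

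Read the 12-week arm contrast from that model. Describe the dropout pattern in the Sample size section in terms of the same model, so that the reader can see which visit is taken as fully retained.

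The model change costs one or two sentences. It needs no new data, visits or participants.

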**Outcomes:**

The primary outcomes, measured at baseline, end of TCFM/placebo, and twelve weeks after, include (1), lower extremity pain, (2) lower extremity functioning, and (3) health-related quality of life. The secondary outcomes, measured throughout the trial process, include (1) recruitment and completion rate (No. of referred, No. of eligible, No. of enrolled, No. of withdrawals, trial recruitment rate, and trial completion rate), (2) participants' safety (No. and severity of adverse events), (3) treatment adherence (average time of each message session, No. of completed sessions, and No. of missed sessions), and (4) compliance (No. of participants completing the trial following the initial group assignment).

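### Three primary outcomes are each tested at two-sided 0.05 with no order, alpha split or success rule, while the sample size spends the full 0.05 on SF-MPQ-2 alone

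*Protocol article*

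**What the plan says.** The Abstract (Outcomes) says that the primary outcomes "include (1), lower extremity pain, (2) lower extremity functioning, and (3) health-related quality of life". The Primary outcome section ties these to SF-MPQ-2, LEFS and SF-36, measured at baseline, at the sixth visit and 12 weeks after the end of the sessions. The numbering is a list; neither place calls it a hierarchy.

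The Statistical analysis section fits an MMRM with each primary outcome in turn as the dependent variable. It then states the comparison: "For each of the outcome, using MMRM, we will compare the difference between the treatment vs. placebo arm in change in mean response". The contrast is taken at one visit only: "in change in mean response from baseline at last visit". The section closes with a single threshold for all analyses, a two-sided P-value "of 0.05 or less will be considered statistical significance".

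The Sample size section considers one outcome, "focusing on the difference in change from baseline at the last visit in SF-MPQ-2 total score", with 80% power at two-sided 0.05, and arrives at 71 per arm (142 in total).

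**The concern.** Read together, these sections define a procedure: three primary tests, each at 0.05, with nothing said about how the three results combine into a conclusion on whether the massage works. The Statistical analysis section also speaks of one primary outcome in one sentence and of several in the next, so the reader cannot tell which result decides the trial.

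The sample size and the analysis do not match. The sample size allots the whole 0.05 to SF-MPQ-2, as one would for a single primary test. The analysis then allots the same 0.05 twice more. At stake is the error rate behind a headline claim of effectiveness. If one significant result out of three can carry that claim, the rate is above 5%. If the lead outcome is chosen after the results are known, error control cannot be recovered.

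**Working it through.** **Step 1: the plan's own figure.** Inputs from the Sample size section: two arms 1:1, power 0.8, two-sided alpha 0.05, 25% dropout at post-baseline visits, compound symmetry with correlation 0.8, SD of change 2. The effect size of 1 is read as a 1-point difference in change.

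The MMRM sample size per arm is n = 2 × φ × (z_0.975 + z_0.80)² × SD² / δ². Here φ is the variance inflation at the last visit from dropout. With everyone seen at baseline and 75% seen at both later visits:

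- φ = (1 − 0.8²)/0.75 + 0.8² = 0.48 + 0.64 = 1.12
- n = 2 × 1.12 × (1.960 + 0.842)² × 4 / 1 = 70.33 (unrounded quantiles), rounded up to 71

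The stated 71 is reproduced. It uses the full 0.05 for SF-MPQ-2 and leaves no alpha for a second or third primary test.

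**Step 2: number of tests.** Three outcomes with one last-visit contrast each give three tests. This is a minimum, because the Primary outcome section gives a 0–100 range for SF-36 but does not name the single score to be tested.

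**Step 3: chance of at least one false positive among the three, when none has an effect.**

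Independent tests: 1 − 0.95³ = 1 − 0.857375 = 0.1426.

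Tests with common correlation ρ, c = 1.96 (the sign of a scale does not matter for two-sided tests):

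1 − ∫ φ(u) [Φ((c − √ρ u)/√(1−ρ)) − Φ((−c − √ρ u)/√(1−ρ))]³ du, where φ(u) is now the standard normal density.

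| Assumed correlation | Error over the three tests |
|---|---|
| 0 | 14.3% |
| 0.3 | 13.6% |
| 0.5 | 12.5% |
| 0.7 | 10.9% |
| 0.8 | 9.8% |
| 0.9 | 8.4% |

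The error passes through 10% at a correlation of about 0.79. The document gives no correlation between the outcomes, so every row is conditional on an assumption.

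**Step 4: what a remedy does to power.** With 71 per arm, the effective number per arm is 71/1.12 = 63.4, and the expected test statistic is 1 / (2 × √(2/63.4)) = 2.815.

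- SF-MPQ-2 alone, or first in a fixed sequence, at 0.05: power = Φ(2.815 − 1.960) = 80.4%. The error over the sequence stays at 5%, because a false positive requires rejecting the first true null in the sequence, which is tested at 0.05.
- Bonferroni at 0.05/3 = 0.0167: power = Φ(2.815 − 2.394) = 66.3%. Keeping 80% needs 2 × 1.12 × (2.394 + 0.842)² × 4 = 93.8 (unrounded quantiles), so 94 per arm (188 in total).

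**The case against.** The best defence is that a journal article may leave multiplicity to an analysis plan that is not shown, and that the 0.05 sentence is a general closing statement which also covers the baseline comparisons. It does not say that one significant primary outcome makes the trial positive. Read outcome by outcome, each test has a 5% error. If all three had to succeed, there would be no inflation at all.

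Part of this stands. A reader might infer that the trial has a false-positive rate of 10–14%. The document does not support that as a fact. It states no any-one-of-three rule, the correlations are assumed, and above a correlation of about 0.79 the figure falls below 10%. The error rates hold only under the reading that any single success counts.

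A reader might also infer that the sixth-visit measurement goes unanalysed. The text does not support that either: the MMRM covers the change at each post-baseline visit, and naming one visit for the comparison limits multiplicity. Nor is sizing a trial on one outcome an error in itself.

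What the defence does not remove is that the article itself fixes three primary outcomes, a test for each, the comparison visit and the threshold. That is a stated procedure and not only a gap. An analysis plan could repair it only by overriding the threshold, changing the status of outcomes named primary, or adding a success rule that is not here. The aim in the Introduction (whether participants feel and function better) and the general effectiveness claim in the Discussion leave it open for one success to carry the conclusion.

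**Conclusion.** The point holds as a mismatch between the Sample size section (one primary test at 0.05) and the Statistical analysis section (three primary tests at 0.05, with no success criterion). Followed as written, the procedure does not hold 5% across the three primary outcomes.

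The size rests on three assumptions: any one significant outcome is taken as success, none of the three has an effect, and the tests share a common correlation. On those terms the error runs from 14.3% under independence to 8.4% at correlation 0.9. If success required all three outcomes, the inflation would vanish; the document does not say so. The 71 per arm is correct for SF-MPQ-2 and is not in question.

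**What to change.** State in the protocol that the between-arm difference in change in SF-MPQ-2 total score at the last visit (12 weeks) is the single primary test at two-sided 0.05. Then test LEFS and one named SF-36 score at the same visit in a fixed sequence, each at 0.05 and only if the one before is significant. Set the sequence, and the SF-36 score, before unblinding. LEFS before SF-36 is one possible order, and the sponsor may reverse it. Sixth-visit contrasts can be reported from the same models as supportive results with confidence intervals.

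This matches the outcome on which the trial is already sized and keeps 142 participants and the SF-MPQ-2 power. Bonferroni would also control the error, but at the loss of power or the larger trial shown in step 4.

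The cost has two parts. There is no confirmatory claim for LEFS or SF-36 if SF-MPQ-2 misses. The change also alters the status of two declared primary outcomes, so it needs a protocol amendment, with ethics committee submission and notice to participants under the Protocol amendments section, and an update of the registry entry.

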### Trial design

This proposed trial is a prospective, double-arm, parallel, double-blinded, randomized controlled trial. Participants, the outcome assessors, and the statistician will be unaware of the group assignment. A one-to-one ratio will help randomly assign participants to the TCFM group or the placebo massage group evenly. Six weekly 25-min TCFM sessions will be delivered to participants in the TCFM group. Six weekly 25-min placebo massage sessions will be delivered to participants in the placebo massage group. Depending on the convenience and preference of participants, the TCFM or placebo massage will be conducted either at participants' homes or in a room provided by University of Houston-Downtown. The trial will be reported following the Consolidated Standards of Reporting Trials (CONSORT) Statement (34). Figure 1 shows the enrolment, interventions, and assessment schedule of this proposed trial.

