### Safety

TCFM is generally safe with the possibility of rare adverse events that might include mild discomfort, soreness, and slight bruising during or after a session (32). The safety measures will include assessment and treatment with monitoring of responses that enable the therapist to adapt the treatment to patient needs. Assessment will include skin inspection of the legs, feet, and toes for lesions, indurations, or damage. The therapist will avoid massaging the areas of skin breakage. Participants will be encouraged to verbalize experiences of increased pain, increased sensitivity in their feet, and additional discomforts of tenderness, nausea, sweating, skin rashes, or extreme fatigue. If the participants complain of increasing pain the therapist will provide more gentle therapy. The therapist will assess any unfavorable participant reactions. The therapist will carefully document these events in the case report form. To avoid the spread of infectious agents, The massage therapist will don latex or nonlatex (for those who are allergic to latex) gloves while performing the massage and perform hand hygiene after each session.

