The secondary outcomes include (1) recruitment and completion rate (No. of referred, No. of eligible, No. of enrolled, No. of withdrawals, trial recruitment rate, and trial completion rate), (2) participant safety (No. and severity of adverse events), (3) treatment adherence (average time of each message session, No. of completed sessions, and No. of missed sessions) and compliance (No. of participants completing the trial following the initial group assignment). Adverse events will be recorded by the therapists in the notes. A published systematic review of the negative effects of massage therapy in the context of pain found the following adverse but rare events which the therapists will be instructed to watch out for, including disc herniation, soft tissue trauma, neurologic compromise, spinal cord injury, vertebral artery dissection, bone fracture, hematoma or hemorrhagic cyst, syncope, cauda equina syndrome, pain, and dislocation (32).

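### Adverse events are summarised only as a total and per participant, so early stoppers count as fully exposed; events per session delivered should be added

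*Protocol article*

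**What the plan says.** In the protocol article:

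- **Summary measure.** Statistical analysis lists "adverse events (in two forms, total number and number per participant" among the descriptive secondary rates. It gives no form per session or per unit of time. The same sentence gives adherence a session denominator (completed over offered sessions).
- **Capture.** The secondary-outcome paragraph under Data collection says "Adverse events will be recorded by the therapists in the notes", and Safety says "The therapist will carefully document these events in the case report form". No other recorder is named. No enquiry is described for people who stop or for the 12-week visit.
- **Window.** The abstract introduces the secondary outcomes, safety among them, with "The secondary outcomes, measured throughout the trial process, include". Safety expects "mild discomfort, soreness, and slight bruising during or after a session".
- **Planned exposure.** Trial design says "Six weekly 25-min TCFM sessions will be delivered to participants in the TCFM group" and plans the same number and length of sessions for placebo.
- **Expected loss.** Sample size assumes "a dropout rate of 25% at post-baseline visits in both arms".
- **Exposure data.** Treatment adherence includes "No. of completed sessions, and No. of missed sessions".

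**The concern.** The risk of soreness or bruising from massage builds up with each massage. The person who would record it meets the participant to deliver the sessions. A count per participant treats everyone as having had the same opportunity for an event and for its recording. That fails once people stop early, and the plan itself allows for a quarter dropping out. The total has the same weakness when the arms are of equal size.

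Participant safety is part of the trial's second aim, so two things are at stake. The absolute figure in each arm may be read as the burden of a six-session course when it describes a shorter average course. If one arm is left earlier or more often, its count also falls for a reason unrelated to the risk of each session. Unequal stopping is plausible, because TCFM includes deeper pressure on tender points and the placebo is gentle rubbing. The article gives no figure for it.

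**Working it through.** **The plan's own figure.** No adverse-event rate is stated, so the figure to reproduce is the sample size, which bears on when dropout is expected.

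- Complete data: n = 2 × SD² × (1.960 + 0.842)² / difference², with SD 2 and difference 1, gives 62.79 per arm.
- With correlation 0.8 and a quarter already missing at the first post-baseline visit (retention 1, 0.75, 0.75), the inflation factor is (1 − 0.8²)/0.75 + 0.8² = 0.48 + 0.64 = 1.12.
- 62.79 × 1.12 = 70.33, rounded up to the stated 71.
- Loss only at the last visit gives 69. Gradual loss (1, 0.875, 0.75) gives 70.

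The stated 71 thus fits a quarter missing by the sixth massage visit. It does not prove this, because a two-visit calculation with retention 0.75 gives the same factor.

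**Exposure within an arm.** Let p be the share stopping before session six and m the mean number of sessions they receive. Mean sessions = (1 − p) × 6 + p × m. With constant risk per session, the shortfall against a full course is 1 − mean/6. Here p = 0.25 is the plan's dropout figure, read as stopping massage early; m is assumed.

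| Timing of stopping (assumed) | m | Mean sessions | Shortfall |
|---|---|---|---|
| All after session one | 1 | 4.75 | 20.8% |
| All after session two | 2 | 5.00 | 16.7% |
| Uniform after 0 to 5 | 2.5 | 5.125 | 14.6% |
| Uniform after 1 to 5 | 3 | 5.25 | 12.5% |
| All after session five | 5 | 5.75 | 4.2% |

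With 71 per arm, stopping after session two means 71 × 5.00 = 355 sessions delivered out of 71 × 6 = 426 planned. Anyone lost only after session six adds nothing to the shortfall.

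**Comparison between arms.** At equal risk per session, the ratio of per-participant figures equals the ratio of mean sessions, whatever the risk is.

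| Stopping, TCFM v placebo (assumed unless equal) | After session one | After session two | After session three |
|---|---|---|---|
| 25% v 25% | 1.00 | 1.00 | 1.00 |
| 25% v 10% | 4.75/5.50 = 0.86 | 5.00/5.60 = 0.89 | 5.25/5.70 = 0.92 |
| 40% v 10% | 4.00/5.50 = 0.73 | 4.40/5.60 = 0.79 | 4.80/5.70 = 0.84 |

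The ratio per session delivered is 1.00 in every cell. A true 20% excess per session in TCFM, with 25% v 10% stopping after session one, would show as 1.2 × 0.864 = 1.04 per participant.

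**Limit of the per-session rate.** Assume 25% of an arm are prone (0.5 events per session) and leave after session one, while 75% have 0.05 per session and complete.

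- True mean risk per session: 0.25 × 0.5 + 0.75 × 0.05 = 0.1625.
- Events per participant: 0.25 × 0.5 × 1 + 0.75 × 0.05 × 6 = 0.35, against 6 × 0.1625 = 0.975 for a full course, or 36%.
- Events per session: 0.35/4.75 = 0.074, against 0.1625, or 45%.

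Here the per-session rate is closer, but still less than half the true risk.

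**The case against.** The strongest reply has five parts.

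- **The capture window is inferred.** A reader might conclude that events are seen only at massage sessions. No passage says so. The abstract has safety measured throughout the trial, and Safety expects some events after a session. This stands: the text supports only that no other route is described. Later capture would not equalise exposure, however, because massage-related risk still depends on the massages received.
- **No biased comparison is planned.** Adverse events are a descriptive rate with no between-arm test, and the plan's own assumption is 25% dropout in both arms. With equal timing that gives a ratio of 1.00. This stands, so between-arm bias is conditional. The equal-dropout assumption was made for power, though, and does not ensure equal stopping in the trial.
- **Events per participant is a legitimate summary.** It describes the burden people actually experienced, and it is too low only against a full course. This stands, and is a reason to keep it.
- **A per-session rate is imperfect.** It misleads if susceptible people leave early, as the last example shows. If events cluster in early sessions, it overstates risk in the arm that stops early. This stands, and is a reason to present it descriptively with a caveat.
- **The analysis plan may cover it.** An exposure-adjusted rate could be added there without contradicting the article. True, but the article does not leave the measure open: it names two forms, and neither reflects exposure.

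**Conclusion.** The point holds as a gap in the stated summary, not as an error in the reported figures. Both adverse-event forms ignore unequal exposure, in a trial that plans for 25% dropout and already counts sessions. If that 25% stop before session six and risk per session is constant, the per-participant figure is about 4% to 21% below that of a full course in both arms. The timing is assumed.

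Between arms, the effect depends on unequal stopping or timing, for which the documents give no figures. At equal risk, assumed splits of 25% v 10% give ratios of 0.86 to 0.92, and 40% v 10% gives 0.73 to 0.84.

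A reader might infer that the arm with more stopping will look safer than the other arm. The documents do not support that. An event that causes someone to stop is still counted if recorded, and a true 20% excess in TCFM would still show as 1.04 in the example above. What can be said is that, with unequal stopping, such an arm looks safer than its own per-session risk. Nor do the documents support replacing the per-participant figure or requiring a Poisson model with a session offset; each of those is a trade-off.

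**What to change.** In Statistical analysis, keep the total and the per-participant figure, and add adverse events divided by sessions delivered, by arm. Present it descriptively with the number of sessions delivered in each arm. Add a sentence saying that this rate does not fully remove bias if susceptible participants stop early or if risk changes across sessions.

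The cost is one or two sentences. Completed sessions are already counted, so no new data are needed, and the sample size and primary analysis are unaffected.
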